### Participants

Children from the 5th and 6th grades will be recruited. Children, instead of adolescents, were selected because it is during childhood that the formation of habits and behaviors takes place [47]. Moreover, unlike children, adolescents are on a developmental stage where a sense of autonomy arises, and many adolescents are resistant to interventions [48, 49]. That is, among adolescents, external control (e.g., parents) of food consumption decreases and internal control becomes increasingly predominant in the face of food choices. Moreover, considering the required degree of autonomy and skills on ICT to partake in the study, the late childhood spectrum seemed more feasible to implement the program.

For the purpose of this study, children attending the regular curriculum will be included. We will seek to exclude children attending alternative curricula, i.e., who have been identified by the school office as having special needs, since these children will not have the necessary autonomy required to attend the program. Additionally, despite the preventive nature of the present program, children will not be included/excluded from the intervention based on their weight status, nor will they need an alteration of their usual care pathways (e.g., medication) to participate in the intervention. Specific inclusion criteria include the following:
Access to a computer equipped with a camera and speakers at home;Internet access at home;Parents have to provide a written consent for their children to participate;Children have to provide a written agreement of willingness to participate;Parents have to be willing to participate in parental involvement activities;Parents have to own an e-mail account or be willing to create one.

### Proposed sample size

Considering this longitudinal design, in the calculation of the sample, we considered a 0.25 effect size, an alpha level of 0.05, a desired statistical power of 0.8, five measures, and three research groups (i.e., control, online intervention, enhanced online intervention). To run a three-level cluster-randomized trial, previous analysis suggested 40 groups per group condition with 15 participants in each, measured at five different time points (see section “Definition of the hierarchical model”).

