Amidst this scenario, information and communication technologies (ICT) are emerging as innovative and potentially cost-effective ways to respond to these challenges. ICT seems to offer the possibility of lowering the costs associated with implementing intervention programs, with the added potential benefit of reaching more individuals. In fact, eHealth interventions are spreading in many domains, including healthy eating or weight management [22]. The results of online tools or web-based programs in promoting healthy lifestyles and behaviors (e.g., fruits and vegetables consumption) and in supporting obesity treatment are very encouraging, with real potential to create a sustained impact on prevention and treatment of obesity [22]. However, despite the increasing number of online interventions on this topic and its potential on behavioral change, there is still a need of further investigation. The results of the majority of these online interventions are unclear; the designs tend to be diverse and the duration of the interventions tends to be short; and, lastly, few interventions include weight loss strategies sustained on a theoretical framework [23]. Also, the actual reach of internet-delivered interventions seems to be lower, and attrition rates higher, than expected, which reinforces the need to further explore this mode of delivering the intervention. Lastly, there are few online interventions focusing on preventive obesity approach by promoting healthy eating strategies among the general population, especially in early stages of life (e.g., children), and not only for individuals at risk or struggling with obesity [24].

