#### The design

This is a 3-arm randomized controlled trial (RCT) with the following: a control group, with no program; an intervention group, with the online narrative-based program; and an enhanced-intervention group, with the online narrative-based program with gamification strategies embedded in the program. Both intervention groups (i.e., the intervention group and the enhanced-intervention group) will have the same narrative-based intervention described in Table 1. The only difference between the two intervention groups is that, in the enhanced online intervention group, gamification strategies will be added to the dynamics of the program. No other intervention components, timings, and materials will differ between these two trial arms. Despite the potential advantages of conducting online interventions, literature on digital interventions to promote behavior change has highlighted that this mode of delivery is associated with high rates of dropout [39]. Thus, one concern among researchers in this field is to devise strategies that mitigate the high rates of dropout and instill engagement in the online intervention [39, 40]. Accordingly, we are implementing the additional gamification strategies in the third group to assess the efficacy of these strategies in promoting engagement with the program and activities.

Gamification consists in the use of game design elements in a non-game context [41]. Non-game contexts can be education [42], health [43], and business [44]. Examples of game design elements are the narrative context, feedback, reputation, ranks, levels, competition, and relational support [41]. Considering the engaging nature of games, it is expected that adding some of their design and motivational features to the non-game contexts [41, 45, 46] will contribute to the (i) creation of engaging and fun contexts or environments, (ii) enhancement of the degree and depth of participants’ engagement, (iii) promotion of learning opportunities, and (iv) motivation of individuals to engage in the task at hand. Table 2 illustrates how gamification was infused in the online program for the enhanced online intervention group.

**Table 2 Tab2:** Gamification elements used in the enhancement-treatment group

Elements*	Objective/rationale**	How it was implemented

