As Heo et al. [54] and others (e.g., [55]) have indicated, the most important goal of a longitudinal intervention is to test whether there are differences between intervention groups with respect to their average growth rates. Applying the approach of these authors, the power to detect a specified treatment difference between average rates of change for the groups is defined as the probability of rejecting the null hypothesis of no treatment-by-linear-trend interaction *H*_0_: γ_101_ = 0, given that it is fact false (γ_101_ ≠ 0). This hypothesis can be tested with
5$$ {F}_o=\frac{{\hat{\gamma}}_{101}^2}{Var\left({\gamma}_{101}\right)}=\frac{\Delta^2\left[{N}_1{N}_2{N}_3 Var(T)\right]}{2\left(1-{\rho}_1\right){\sigma}^2{N}_1 Var(T){\sigma}_{u1}^2}, $$

where Δ is the effect standardized effect size at the last time point, *N*_1_ is the number of level 1 units (repeated measures) per student, *N*_2_ the number of level 2 units (students) per classroom, *N*_3_ the number of level 3 units (classroom) per treatment condition, *Var*(*T*) is the population variance of the time variable *T*, $$ {\upsigma}_{u1}^2 $$ is the three-level random slope variance, σ^2^ is the sum of the other variances, and *ρ*_1_ is the correlation between outcomes measures at different time points on the same student nested within classroom.

The power of the test statistic *F*_0_, denotes 1 − *β*, can be written as follows:
6$$ 1=\beta =\phi \left\{{\left\{\frac{\Delta }{\left({N}_1-1\right)}\left[\frac{\left[{N}_1{N}_2{N}_3 Var(T)\right]}{2\left(1-{\rho}_1\right){\sigma}^2{N}_1 Var(T){\tau}_s}\right]\right.}^{\frac{1}{2}}-{Z}_{1-\left(\alpha /2\right)}\right\}, $$

where τ_*s*_ is the ratio of the three-level random slope variance to the sum of the other variances, ϕ is the cumulative distribution function of a standard normal distribution, and *Z*_1 − (α/2)_ is the 100 (1 − *α*/2) percentile of the standard normal distribution for a bilateral test.

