Consider the following hypothetical values for three-level cluster-randomized trial design parameters: $$ {\upsigma}_e^2=0.5 $$, $$ {\upsigma}_{r0}^2=0.3 $$, $$ {\upsigma}_{r1}^2=0.0 $$, $$ {\upsigma}_{u0}^2=0.2 $$, and $$ {\upsigma}_{u1}^2=0.1 $$. Under the fixed slopes model, the correlation between the outcomes from different student nested within the same classroom is $$ {\uprho}_2={\upsigma}_{u0}^2/\left({\upsigma}_e^2+{\upsigma}_{r0}^2+{\upsigma}_{u0}^2\right)=0.2 $$, whereas the correlation between the outcomes measured at different time points on the same students nested within classrooms is $$ {\uprho}_1={\upsigma}_{r0}^2+{\upsigma}_{u0}^2/\left({\upsigma}_e^2+{\upsigma}_{r0}^2+{\upsigma}_{u0}^2\right)=0.5 $$. Further assumptions are as follows: (a) number of classrooms per treatment condition: *N*_3_ = 40; (b) average number of students per classroom: *N*_3_ = 15; (c) number of repeated measures per student: *N*_1_ = 5; (d) alpha significance level: *α* = 0.05; and (e) statistical power: 1 − *β* = 0.80.

Given design parameters and further assumptions, the minimum detectable effect size is 0.25. In our opinion, an effect size of Δ = .25 is a good first estimate of the smallest effect size of interest in psychological research, since it is not irrelevant and requires a considerable sample size to detect a treatment effect predicted by the researcher.

Finally, we consider that a study with 80% power is a properly powered study, despite several researchers (see, e.g., [56]) consider this a value rather low, as it entails a 20% chance of not finding a theoretically important finding.

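### The 80% power at an effect of 0.25 is a zero-loss figure: enrolment equals the number the calculation needs, with no allowance for missed assessments

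*Protocol article*

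**What the plan says.** Under Proposed sample size the protocol reports that "we considered a 0.25 effect size, an alpha level of 0.05, a desired statistical power of 0.8, five measures, and three research groups", and that "previous analysis suggested 40 groups per group condition with 15 participants in each, measured at five different time points". The section Definition of the hierarchical model prints the whole calculation. It enters "number of classrooms per treatment condition: *N*_3_ = 40" and "average number of students per classroom: *N*_3_ = 15" (the second symbol is plainly meant to be N2), with five repeated measures per child, and concludes: "Given design parameters and further assumptions, the minimum detectable effect size is 0.25". The abstract gives 40 groups of about 15 children per arm as the number to be recruited.

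On attrition, The design says that "this mode of delivery is associated with high rates of dropout". The introduction's Background describes internet-delivered interventions as having "attrition rates higher, than expected". The Discussion presents gamification as a means of reducing attrition. No section gives an expected rate of loss or an inflation of the sample.

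**The concern.** The recruited number and the number entered in the calculation with complete data are the same. Any missing assessment therefore takes the trial below its stated power, in a document that treats attrition as a known difficulty of online delivery and justifies its third arm partly by it.

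The figure carries weight. The protocol treats 0.25 as its smallest effect of interest, accepts a 20% chance of missing it, and in the Discussion offers the a priori power analysis as mitigation of a small sample. If the true chance of missing 0.25 is larger, a null result would be read as stronger evidence against such an effect than it is.

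**Working it through.** **Inputs.** From Proposed sample size and Definition of the hierarchical model: effect Δ = 0.25 at the last time point, alpha 0.05 two-sided ("percentile of the standard normal distribution for a bilateral test"), N1 = 5, N2 = 15, N3 = 40, ρ1 = 0.5, residual variance 0.5, child intercept variance 0.3, classroom intercept variance 0.2 (so σ² = 1.0), slope variance σ²u1 = 0.1. Assumed: Var(T) = 2, for five equally spaced times coded 0 to 4, since the protocol gives no value.

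**Formula.** The power equation with the plus sign restored in its denominator (as printed it is a product, probably a typesetting loss):

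power = Φ{ Δ/(N1 − 1) × √[ N1·N2·N3·Var(T) / (2[(1 − ρ1)σ² + N1·Var(T)·σ²u1]) ] − 1.960 }

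**Step 1: the stated figure.**
- Numerator: 5 × 15 × 40 × 2 = 6000.
- Denominator: 2 × (0.5 + 5 × 2 × 0.1) = 3.
- √(6000/3) = 44.72; divided by 4 = 11.18.
- Power = Φ(0.25 × 11.18 − 1.960) = Φ(0.835) = 0.798.
- Detectable effect at 80% = (1.960 + 0.842)/11.18 = 0.2506.

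This matches the stated 80% at 0.25, and only with all 15 children and all five measures.

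**Step 2: whole-child loss in both compared arms.** Replace N2 by 15(1 − d).
- d = 20%: √(4800/3)/4 = 10.00; power Φ(0.540) = 0.705; detectable effect 0.280.
- d = 30%: √(4200/3)/4 = 9.354; power Φ(0.379) = 0.648; detectable effect 0.300.
- d = 40%: √(3600/3)/4 = 8.660; power Φ(0.205) = 0.581; detectable effect 0.324.

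**Step 3: gradual loss, partial data kept.** Children who drop out do so in equal shares after each of the first four visits, and their earlier data enter the mixed model. The variance of the mean slope in one arm comes from the generalised least squares information, with the 0.1 slope variance between children as in Step 1. It is 0.000250 at zero loss and 0.000287, 0.000310 and 0.000338 at 20, 30 and 40% loss. Power = Φ{ (0.25/4)/√(sum of the two arms' variances) − 1.960 }. For example, at 20% loss:
- both arms: 0.0625/√(2 × 0.000287) = 2.61, power 0.741;
- programme arm only: 0.0625/√(0.000250 + 0.000287) = 2.70, power 0.769.

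| Assumed loss | Gradual, programme arm only | Gradual, both arms (detectable effect) | Whole-child, both arms (detectable effect) |
|---|---|---|---|
| 0% | 80% | 80% (0.25) | 80% (0.25) |
| 20% | 77% | 74% (0.27) | 71% (0.28) |
| 30% | 75% | 71% (0.28) | 65% (0.30) |
| 40% | 73% | 67% (0.29) | 58% (0.32) |

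**Step 4: how firm the base figure is.** Two separate points move it.
- The protocol defines σ²u1 as a classroom-level slope variance and sets the child-level one to zero. The slope term should then also be multiplied by N2: the denominator becomes 2 × (0.5 + 5 × 15 × 2 × 0.1) = 31, and power is 0.138. At 40% whole-child loss it is 0.136, so dropout hardly matters on that reading.
- Table 3, Anthropometric measures, and Primary and secondary outcome measures list four occasions (baseline, final, 3 and 6 months); the abstract adds a 9-month follow-up. With four visits coded 0 to 3 and the same variances, the Step 1 formula gives about 0.90. That change depends wholly on how time is scaled.

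**The case against.** The strongest objection is that the attrition statements concern online programmes, not outcome data. Children complete the assessments on-site (Blinding and data access), the research team takes the body measurements, and consent is sought to use the data of those who withdraw. Workshops are offered to promote follow-up completion. A child who stops using the platform can still be assessed. This stands. A reader might infer that the protocol expects 20 to 40% of its own outcome data to be lost; it says no such thing, and the range is an assumption made here.

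The control arm has no programme to leave, and the planned linear mixed model can use incomplete records. This also stands. Equal whole-child loss in both arms is a worst case, so 71/65/58% should not be quoted as the likely power.

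It can also be said that nothing is miscalculated and that a condensed article may leave a retention assumption to the full protocol or SAP. The first part is right: the figure reproduces. The second does not remove the point. The article prints the full calculation and the recruitment target, and because the two numbers coincide, the allowance is fixed at zero. The Discussion's warning about a small sample softens the risk of over-reading a null result, but does not attach the zero-loss condition to the 80%.

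**Conclusion.** The point holds as a conditional one. The 80% power at 0.25 is correct on the plan's reading of its formula only at zero loss, and the enrolment leaves no margin: with whole-child loss in both arms, about 4.5% is enough to bring power below 78%.

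The direction is certain; the size is not, since no assessment-loss rate is given. Over an assumed 20 to 40% gradual loss, the shortfall is about 3 to 7 percentage points if only the programme arm loses children and 6 to 13 if both compared arms do.

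The stronger reading, that the trial will fall to 58 to 71% power, is not supported. It needs equal loss in a control arm without a programme, no use of partial data, and programme dropout treated as missed assessment.

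All these percentages rest on Var(T) = 2, five visits, and a slope variance that acts between children. The last two are in doubt in the protocol itself, so the figures show sensitivity to loss and are not final power values.

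**What to change.** Keep the planned enrolment. In Proposed sample size and in Definition of the hierarchical model:

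- state the expected assessment retention for each arm, separately from programme adherence;
- give power and minimum detectable effect at that retention, beside the zero-loss figure;
- label 80% at 0.25 as the zero-loss value.

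Do this after settling whether the slope variance lies at classroom or child level and whether there are four or five visits, because both change the base figure. The cost is a few sentences and a slightly less favourable stated figure; no further participants are needed.

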### Assessment

Table 3 illustrates the timeline for the different assessment measures of the children participating in this project.

**Table 3 Tab3:** Timeline for the different assessment measures of the project

Measures	Registration (−T1)	Baseline assessment (T0)	Final assessment (T1)	3-month follow-up assessment (T3)	6-month follow-up assessment (T4)	Weekly assessment
Eligibility screen	X	–	–	–	–	–
Informed consent	X	–	–	–	–	–
Anthropometric	X	–	X	X	X	–
Sociodemographic	X	–	X	X	X	–
Self-Regulation^1^	–	X	X	X	X	–
Self-efficacy^2^	–	X	X	X	X	–
Declarative knowledge^3^	–	X	X	X	X	–
Attitudes and perceptions^4^	–	X	X	X	X	–
Healthy eating and physical activity behaviors^5^	–	X	X	X	X	–
Satisfaction	–	–	Intervention groups	–	–	–
Journal	–	Control group	Control group	–	–	Intervention groups

*X* available to all groups

^1^Self-Regulation Processes towards Healthy Eating Questionnaire

^2^ Self-Efficacy to Regulate Eating Habits for Children Questionnaire & Healthy Eating and Physical Activity Self-Efficacy questionnaire for children

^3^ Knowledge of Healthy Eating Questionnaire

^4^Students’ Attitudes and Perceptions on Healthy Eating Questionnaire

^5^ Healthy Eating and Physical Activity Behavior Recall Questionnaire for Children

### Anthropometric measures

Children participating in the intervention and control groups will have their weight, height, and waist circumference measured by the research team at the baseline, post-intervention, and at the 3- and 6-month follow-ups. This trial does not involve collecting biological specimens for storage.

### Self-report questionnaires

#### Sociodemographic measures

These measures will include questions about participants’ sex, age, grade, academic achievement, and socioeconomic level, as well as questions about other healthy habits and behaviors, such as their daily screen time and physical activity.

#### Psychological self-report measures

##### Self-Regulation Processes towards Healthy Eating Questionnaire

An adapted version of *Self-Regulation for Health* scale [50] will be used to assess the SR processes towards healthy eating. This measure consists of nine statements regarding the participants’ self-regulation towards healthy eating (e.g., “I plan my meals. I think about what I’m going to eat and what it takes to prepare my meal”). Responses to the individual items are scored from 1 (never) to 5 (always) in a Likert-like scale and summed to create a composite score ranging from 9 to 45, with higher scores implying more self-regulation.

##### Healthy Eating and Physical Activity Self-Efficacy questionnaire for children (HEPASEQ-C)

An adapted version of the HEPASEQ-C will be used to assess self-efficacy related to enacting healthy eating and activity behaviors in children [51]. This version consists of nine items, with seven focusing on self-efficacy related to healthy eating (e.g., “I will eat healthy food even when my friends eat food that is not healthy.”), and two focusing on self-efficacy related to physical activity (e.g., “I am physically active for 60minutes/ 1 hour per day”). Responses to the individual items are on a Likert-like scale, ranging from 1 (There is no way I can do this) to 5 (I am definitely sure that I can do this) and summed to create a composite score ranging from 9 to 45, with higher scores implying more self-efficacy. Also, a sixth option was added when the situation is not applicable. This answer does not contribute to the composite score.

##### Healthy Eating and Physical Activity Behavior Recall questionnaire for Children

This measure was developed as a complement to the HEPASEQ-C questionnaire and aimed to recall children’s behaviors in terms of healthy eating and physical activity [51]. The adapted version of this questionnaire consists of 19 items. Five items are in an open response format allowing children to write the actual foods they ate (e.g., “Last time I had a meal at a friend’s place I ate…”). Six items are yes/no response options (e.g., “I eat breakfast every day”). For the remaining eight items, responses were provided via writing down a number (e.g., “Over the last 3 days I drank … soda beverages”). Frequencies of responses to the individual items will be analyzed (e.g., percentage of students that eat breakfast, percentage of students that choose healthy options at friends’ home).

##### Self-Efficacy to Regulate Eating Habits for Children

An adapted version of the questionnaire “Self-Efficacy to Regulate Eating Habits” developed by Bandura [52] will be used to assess student’s perceived capability to regulate and to adopt healthy eating habits in different daily situations (e.g., “While watching television”). This version consists of 17 adapted situations/scenarios, plus the option of providing other examples, in which participants will have to respond if they can choose healthy food choices or not. Responses to the individual items are presented in a Likert-like format, scored from 1 (not capable) to 5 (capable, for sure) and are summed to create a composite score ranging from 17 to 85, with higher scores implying more self-efficacy to regulate eating habits. Also, a sixth option was added when the situation is not applicable. This answer does not contribute to the composite score.

##### Attitudes and Perceptions on Healthy Eating Questionnaire

An adapted version of the Students’ Attitudes and Perceptions on Health Instrument [50] will be used to assess students’ attitudes and perceptions towards healthy eating. This measure consists of 17 statements about student’s attitudes and perceptions of the importance of healthy eating (e.g., “Eating fruit and vegetables will help me growing up”). Responses to the individual items are presented in a Likert-like format, scored from 1 (I completely disagree) to 5 (I completely agree) and are summed to create a composite score ranging from 17 to 85, with higher scores implying more positive attitudes and perceptions about healthy eating. Also, a sixth option was added when the situation is not applicable. This answer does not contribute to the composite score.

